#### Fatigability during the cognitive task

3.4.5

Fatigability during the cognitive task (Research Question 2) will be quantified as reported by Hassan et al. (2024) using the balanced integration score (BIS) (Liesefeld & Janczyk, 2019). The AX‐CPT was chosen as the task in which to measure task performance, and therefore it will be presented first and last, following the protocol of Hassan et al. (2024). The BIS will be calculated using the reaction time and response data during the first and last repeat of the AX‐CPT task. The BIS combines reaction time and accuracy into a single metric which is standardized across all time points and participants. A BIS score of zero represents an average level of performance across all participants and conditions, with above average and below average performance indicated by positive and negative numbers, respectively. The code used to calculate the outcome measure is available at https://github.com/Liesefeld/BIS.

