#### Fatigability during the physical task

3.4.6

Fatigability during the 6MWT (Research Question 2) will be quantified as the change in average walking speed (m/s) from the beginning (30−60 s) to the end (330−360 s) of the test (Andersen et al., 2016; Witherspoon et al., 2018). The first time point will be taken after the initial 30 s to avoid confounding from acceleration. Example data and the code used to calculate fatigability in during the 6MWT are provided as Supporting information.

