Hypothesis 2: State fatigue following exertion will be predicted by somatosensory attenuation at baseline, somatosensory gating at baseline, the presence of long COVID (long covid/controls), and the type of task (cognitive/physical). Performance fatigability will be considered a moderator variable in these relations. State fatigue prior to exertion will be included as a covariate in this analysis.

This will be tested using a linear mixed model:

$$Y_{ijk}=\mu +a_{i}+b_{j}+c_{k}+d_{ik}+e_{ik}+f_{ik}+g_{ijk}+\left(f_{ik}\times a_{i}\right)+\left(f_{ik}\times b_{j}\right)+\varepsilon_{ijk}$$
where:

*Y_ijk_
*: state fatigue following exertion in the *i*‐th group (long COVID/control) during task *j* (cognitive/physical) for the *k*‐th subject.μ: the overall mean of state fatigue following exertion.
*a_i_
*: the effect of the *i*‐th group (fixed effect: long COVID vs. control).
*b_j_
*: the effect of the *j*‐th task (fixed effect: cognitive vs. physical).
*d_ik_
*: the baseline somatosensory attenuation for the *k*‐th subject in the *i*‐th group.
*e_ik_
*: the baseline somatosensory gating for the *k*‐th subject in the *i‐*th group.
*f_ijk_
*: the performance fatigability for the *k*‐th subject in the *i*‐th group during the *j*‐th task.
*g_ijk_
*: the state fatigue prior to exertion for the *k*‐th subject in the *i*‐th group during the *j*‐th task (covariate).(*f_ik_
*×*a_i_
*): the interaction term between performance fatigability and group.(*f_ik_
*×*b_j_
*): the interaction term between performance fatigability and task.
*ϵ_ijk_
*: the residual error term, assumed to be normally distributed.
Hypothesis 3: The change in somatosensory attenuation (Research Question 3a) and somatosensory gating (Research Question 3b) from pre‐ to post‐task will be predicted by the change in state fatigue from pre to post, fatigability, the presence of long COVID (long COVID/controls), and the type of task (cognitive/physical).

We will use linear mixed models to test these hypotheses, with separate models for somatosensory attenuation and somatosensory gating:

$$Y_{ijk}=a_{i}+b_{j}+c_{ijk}+d_{ijk}+u_{0i}+\varepsilon_{ijk}$$
where:

*Y_ijk_
*: attenuation or gating at baseline in the *i*‐th group (long COVID/control) during task j (cognitive/physical) for the k‐th subject.
*a_i_
*: the fixed effect of the *i*‐th group (long COVID vs. control) on baseline attenuation.
*b_j_
*: the fixed effect of the *j*‐th task (cognitive vs. physical) on baseline attenuation.
*c_ijk_

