*: the change in state fatigue from pre to post in the *i*‐th group, during task *j*, for the k‐th subject, affecting baseline attenuation.
*d_ijk_
*: the change in fatigability in the *i*‐th group, during task *j*, for the *k*‐th subject,
*u*
_0_
*
_i_
*: random intercept for group *i*, capturing group‐level variability
*ϵ_ijk_
*: residual error term, representing random variability and measurement error not explained by the fixed effects.
Hypothesis 4: Among individuals with long COVID, trait fatigue will be effected by mood, illness beliefs, autonomic symptoms, increase in state fatigue induced by a physical task, the increase in state fatigue induced by a cognitive task, and autonomic nervous system function.

This will be tested using a linear mixed effects model:

$$Y_{i}=\mu +a_{i}+b_{i}+c_{i}+d_{i}+e_{i}+f_{i}+u_{0i}+\varepsilon_{i}$$
where:

*Y_i_
*: trait fatigue for individual *i*.μ: the overall mean of state fatigue following exertion.
*a_i_
*: mood for individual *i*.
*b_i_
*: illness beliefs for individual *i*.
*c_i_
*: autonomic symptoms for individual *i*.
*d_i_
*: change in state fatigue induced by physical task for individual *i*.
*e_i_
*: change in state fatigue induced by cognitive task for individual *i*.
*f_i_
*: autonomic nervous system function for individual *i*

*u*
_0_
*
_i_
*: random intercept capturing individual‐specific variability in trait fatigue not explained by the fixed effects.
*ϵ_i_
*: residual error term representing random variability and measurement error.

We will check the following assumptions of the regression models: linearity, independence, homoscedasticity, normality and multicollinearity.

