### Sample size

3.8

The study is powered to address Research Question 1a. Previous research indicates an effect size of 0.78 for differences in somatosensory attenuation between young and older individuals (Parthasharathy et al., 2022). Powering the current study to detect an effect size of 0.78 between two independent means for Research Question 1a—somatosensory attenuation in individuals with and without long COVID—with an α error probability of 0.05 and a power of 95% and based on a non‐directional two‐tailed hypothesis requires 44 participants per group (G*power 3.1.9.7). Dropout is not expected to impact Research Question 1a or 1b, as it involves initial measurements during the first session. However, there is a potential for dropout to impact the subsequent research questions, which rely on participants returning for a second session.

The sample size gives us power of 90% to detect an effect of 0.70 between two groups at two repeated time points with alpha error probability of 0.05 for Research Questions 2 and 3, or a power of 80% to detect an effect of 0.60. A dropout rate of 10% would mean that our power to detect these effect sizes decreases to 60%. The approach for addressing Research Questions 2 and 3 ensures that the study is adequately powered to detect correlations of 0.50 and 0.40, respectively. The code used to calculate the outcome measure is available at https://github.com/smancuso/R‐ Code/blob/cc90c623c4dc733fe5c93ef5a795dde010152c63/Power.R

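### The Research Question 3 model pools a unitless cognitive fatigability score and a walking-speed change in m/s under one slope, so that slope mainly reflects the cognitive task

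*Protocol article*

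**What the plan says.** **Measures.** Section 3.4.5 takes cognitive fatigability from the first and last AX-CPT using the BIS: "The BIS combines reaction time and accuracy into a single metric which is standardized across all time points and participants". Section 3.4.6 takes physical fatigability as the "change in average walking speed (m/s) from the beginning" to the end of the 6-minute walk. Table 1 gives the same definition as end minus start. The article states no rescaling of the speed change.

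**Research Question 3 (RQ3).** In section 3.7, the model for Hypothesis 3 is a sum of group, task, change in state fatigue, fatigability, a random intercept and a residual. Fatigability enters once, as "the change in fatigability in the" given group, task and subject. It has no interaction with task.

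**Research Question 2 (RQ2).** The model for Hypothesis 2 uses the same variable with two interactions: "the interaction term between performance fatigability and task" and "the interaction term between performance fatigability and group". It has no three-way term.

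**Reruns.** The planned exploratory reruns (section 3.7.1) add age, time of day and session order. None of them separates fatigability by task.

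**The concern.** With both tasks in one model and one fatigability slope, one BIS unit is treated as equivalent to 1 m/s. The slope has no interpretable unit, and the task with the larger numerical spread dominates it. A score built by standardising should have a spread of order 1. A change in walking speed within six minutes is likely to vary by a fraction of a metre per second. The fitted slope would then be close to the cognitive slope, whatever happened on the treadmill.

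This matters because the introduction says it is unclear whether the physical and cognitive dimensions of fatigue share mechanisms, and RQ3 names both fatigability and task type as predictors. A null fatigability result could be read as covering walking when it carries little information about it. A positive result could be credited to both tasks when it comes from one. The RQ2 fatigability×group coefficient has the same weakness, although the main fatigability slope in RQ2 is free to differ by task.

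**Working it through.** **The plan's own figures.** For Research Question 1a (effect 0.78, two-sided 0.05, power 95%), the exact t calculation gives 0.947 at 43 and 0.951 at 44 per group, so 44 reproduces. The figures for RQ2 and RQ3 (90% for 0.70, 80% for 0.60) reproduce as an ordinary two-group t test at 44 per group: 0.901 and 0.795. They are group-comparison powers and do not describe the fatigability coefficient. The same section mentions correlations of 0.50 and 0.40 without saying which predictor they concern.

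**Inputs.** From the article: 44 per group, hence 88 participants, two tasks each, two-sided 0.05. Assumed, because the article gives none: SD of BIS change s_c = 0.5–1.4, SD of speed change s_p = 0.05–0.2 m/s, residual SD 1. The printed random intercept is indexed by group; the simulations below use a subject-level intercept.

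**Weight of each task.** With a task main effect in the model and fatigability unrelated across tasks, the pooled slope weights each task by its fatigability variance. The physical share is s_p² / (s_p² + s_c²).

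| s_c | s_p (m/s) | physical share |
|---|---|---|
| 1.4 | 0.05 | 0.0025/1.9625 = 0.1% |
| 1.0 | 0.1 | 0.01/1.01 = 1.0% |
| 1.0 | 0.2 | 0.04/1.04 = 3.8% |
| 0.5 | 0.2 | 0.04/0.29 = 13.8% |

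**Power for a physical-only effect of 0.35 outcome SD per SD of fatigability.** Ignoring within-subject correlation, the noncentrality is 0.35 × √(88 × share), and power is Φ(λ − 1.96) + Φ(−λ − 1.96).

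- s_c 1.4, s_p 0.05: λ = 0.117, power 5%.
- s_c 1.0, s_p 0.1: λ = 0.327, power 6%.
- s_c 0.5, s_p 0.2: λ = 1.219, power 23% (24% in a simulation with within-subject correlation 0.3).
- Task-specific slope (share = 1): λ = 3.283, power 91%. Simulations with correlation 0.3 gave 89–92%.

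**Simulation over a wider grid** (88 participants × 2 tasks, correlation 0.3, physical-only effect 0.4, s_c 0.7–1.5, s_p 0.05–0.3).

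- Planned single slope: 0.04–0.33.
- One slope after standardising within task: 0.73–0.78.
- Task-specific slope: 0.96–0.97.

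**Effects of opposite sign** (+0.4 cognitive, −0.4 physical, SDs 1.0 and 0.1). The expected pooled slope is (0.4 × 1.0 − 0.4 × 0.1)/(1.0² + 0.1²) = 0.36/1.01 = 0.36, which has the cognitive sign. It was significant in 90% of simulated trials.

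**Same effect in both tasks** (0.3 per SD, SDs 1.0 and 0.1). Planned slope 0.875; one slope standardised within task 0.98; each task-specific slope 0.81–0.82.

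**No effect.** The planned slope rejects in 0.047 of trials.

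**RQ2 fatigability×group** (physical-only interaction 0.6). As planned: 0.05 at SDs 1.0/0.1 and 0.21 at 0.7/0.3. Standardised within task but still shared: 0.51–0.52. Task-specific interaction: 0.81.

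**The case against.** **The full analysis plan may settle scaling.** Scaling and centring of predictors are often left to it, and the printed equations are schematic, with no explicit coefficients. That is fair for scaling alone. But the article prints each model term by term, and it includes fatigability×task for RQ2 while leaving it out for RQ3. A single slope is the natural reading, and z-scoring would still force one common slope.

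**The size rests on assumed SDs.** This stands. A reader might infer that physical fatigability is effectively untested. The article does not support that: it gives no SDs, and at the favourable end of the ranges (0.5 and 0.2, or 0.7 and 0.3) the planned slope retains roughly a quarter to a third of the power. If the effect per SD were the same in both tasks, the planned slope would usually detect it, though mostly from cognitive data.

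**Table 1 lists cognitive fatigability only as the BIS.** A reader might infer that a performance level is being compared with a change. The introduction defines fatigability as a change in performance, section 3.4.5 uses the first and last AX-CPT, and the RQ3 term is described as a change. Only the subtraction is unwritten. A last-minus-first BIS would also run in the same direction as the speed change.

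**The study is powered for Research Question 1a.** This also stands. That comparison contains no fatigability term, and RQ3 keeps its group, task and state-fatigue terms.

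**Conclusion.** The point holds as a fault in a stated secondary model. The mismatch of units and the absence of fatigability×task in RQ3 follow from the text with no assumption beyond the natural reading of the equation, as does the shared fatigability×group coefficient in RQ2. The consequence is a slope that mainly describes the cognitive task: a physical share of about 0.1–14%, and detection of a physical-only 0.35 SD effect in about 5–24% of trials against about 90%. Those figures depend on the assumed SDs and on an effect confined to walking. Where effects of similar size per SD differ in sign, the coefficient reports the cognitive one. False-positive risk for the pooled test is not raised, and the primary comparison is not affected. This is a should-fix, to be settled before the data are analysed.

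**What to change.** 1. **RQ3:** add fatigability×task, or fit the two tasks separately, and report a fatigability slope for each task.
2. **RQ2:** add fatigability×group×task, or fit the tasks separately. Standardising alone would still force the group difference to be equal in both tasks.
3. **Definition:** state that cognitive fatigability is the last minus the first AX-CPT BIS.
4. **Pooled coefficients:** if one is still wanted, z-score fatigability within task over all participants first. The task-specific tests do not depend on scale, so the gain comes from the interaction rather than from the rescaling.

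The cost is one extra term in each model and no new data. Some power is given up if the effects really are common to both tasks: in the 0.3-per-SD example, 0.81–0.82 for each task-specific slope against 0.875 for the planned slope and 0.98 for one slope standardised within task. A standardised pooled slope reported beside the task-specific ones would recover that.

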#### Planned exploratory analysis

3.7.1

Hypotheses 1, 2, 3 will be rerun with age included as a covariate.Hypotheses 1, 2, 3, 4 will be rerun with time of day (morning/afternoon) at which participants completed sessions and session order (cognitive/physical first) included as additional predictor variables.The effect of autonomic dysfunction during exertion, on state fatigue pre‐ to post‐exertion, via an effect on somatosensory processing post‐exertion will be tested using mediation analysis with separate models for somatosensory attenuation and somatosensory gating. This will be quantified in participants with and without long COVID.The relations between autonomic dysfunction during exertion, state fatigue during exertion, and perceived effort during exertion will be quantified in participants with and without long COVID during both tasks (cognitive/physical). This will be tested using correlation analysis.Test‐retest reliability will be conducted for each somatosensory processing measure (gating and attenuation), from the baseline measure from each session (cognitive/physical). This will provide a measure of whether somatosensory processing is stable over time.

We will carry out outcome neutral criteria that must be met for successful testing of the stated hypothesis. This includes checking for the absence of floor or ceiling effects. This will be done by examining data distributions to ensure that there are no extreme values that could impact the validity of results. Additionally, we will investigate the quality of the data and this will include frequency measures and the shape of the distribution.

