### Participants and recruitment

3.2

Participants will be recruited via convenience sampling from the local community using passive recruitment methods (digital and physical posters and announcements). Recruitment will be targeted to match long COVID and control groups for age and gender. To be eligible, individuals must be between 18 and 69 years old. Somatosensory attenuation and gating change with age (Parthasharathy et al., 2022), particularly after the age of 69 years (Timar et al., 2023). This age group will therefore be excluded, to prevent age‐related effects on somatosensory attenuation and gating confounding the results. Participants must be able to speak and understand English and be able to provide informed consent. Participants will be excluded if they have any physical or psychiatric condition that would prohibit them from walking safely on a treadmill, taking part in a cognitive task or completing the full battery of assessments (Supporting information, Appendix 1).

For inclusion in the control group, individuals may have previously tested positive for COVID‐19 but must have been clear of all symptoms by 12 weeks following acute infection and must not report any ongoing fatigue. Participants in the control group must not report any underlying condition that interferes with their daily function. All inclusion and exclusion criteria will be evaluated by self‐report measurements (Supporting information, Appendix 1).

For inclusion in the long COVID group, individuals must self‐report a confirmed COVID infection (confirmed by positive lateral flow test or polymerase chain reaction test, or a clinical diagnosis) and report signs and symptoms that continued or developed 12 weeks or more after acute COVID‐19 infection (National Institute for Health & Care Excellence, 2020). As this study will focus on the impact of fatigue, individuals must report fatigue (physical, cognitive, mental, emotional, psychosocial fatigue or post‐exertional malaise) as one of their long COVID symptoms and must not have experienced any form of ongoing fatigue prior to COVID infection (Supporting information, Appendix 1).

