#### Autonomic nervous system function

3.4.4

Autonomic nervous system function will be quantified using heart rate variability (HRV), calculated as the proportion of successive intervals which differ by >50 ms (Baker et al., 2023). Heart rate will be measured using a polar H10 Hartslagsensor (Polar) streamed into Dflow software (Motek Medical). HRV will be measured during the somatosensory attenuation measure to ensure that participants are sitting quietly, not engaged in trial activity. This will replicate previous measurement in individuals with long COVID to allow comparison (Baker et al., 2023). HRV will additionally be measured throughout the cognitive and physical tasks to allow exploratory analysis of the change in autonomic nervous system function during exertion. HRV measured over a short period mostly reflects parasympathetic nervous system activity (Gullett et al., 2023). HRV has been used as a measure of autonomic nervous system function to quantify autonomic function changes in response to various interventions (Ali & Chen, 2023). Example code used to calculate HRV is provided as Supporting information.

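### Hypothesis 4 (trait fatigue within the long COVID group) is the only hypothesis with no age-adjusted version, so no planned analysis could show whether an autonomic association is partly an age gradient

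*Protocol article*

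**What the plan says.** Section 3.7 sets Hypothesis 4 within one group: "Among individuals with long COVID, trait fatigue will be effected by mood, illness beliefs, autonomic symptoms", together with the fatigue increases from the two tasks and autonomic function. The equation has six predictors. They include "change in state fatigue induced by physical task for individual" and "autonomic nervous system function for individual". Section 3.4.4 defines the latter: "Autonomic nervous system function will be quantified using heart rate variability (HRV". Age is not a term.

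Section 3.7.1 then lists two sets of reruns:
- Age: "Hypotheses 1, 2, 3 will be rerun with age included as a covariate".
- Session conditions: "Hypotheses 1, 2, 3, 4 will be rerun with time of day", and also with session order.

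On age in the design, section 3.2 states "To be eligible, individuals must be between 18 and 69 years old" and aims recruitment at matching the two groups on age and gender. Its stated reason for attending to age is that attenuation and gating change with age. Section 3.4.1 describes the questionnaire measures as serving exploratory analyses for Research Question 4.

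**The concern.** Every predictor in Hypothesis 4 is a difference between people, observed across an age span of 69 - 18 = 51 years. Matching long COVID participants to controls balances age between groups but leaves the whole age spread inside the long COVID group, which is the only group this model uses.

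The introduction assigns the role of the autonomic nervous system in trait fatigue to Research Question 4. The other autonomic analyses in section 3.7.1 concern state fatigue and perceived effort, so Hypothesis 4 is the one place where autonomic function is tested against trait fatigue. If older participants tend to have lower heart rate variability and also more (or less) trait fatigue, the heart rate variability coefficient absorbs part of that age gradient. The reader of the results would have no planned analysis with which to separate the two. An age-adjusted version added after the data are seen would not carry the weight of a planned one in a registered report.

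**Working it through.** **1. What is and is not adjusted for age.**

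| Hypothesis | Age term in main model | In age rerun | In time-of-day and session-order rerun |
|---|---|---|---|
| 1 | no | yes | yes |
| 2 | no | yes | yes |
| 3 | no | yes | yes |
| 4 | no | **no** | yes |

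**2. Sample available.** Section 3.8 gives 44 per group for a standardised difference of 0.78, two-sided 5%, 95% power. The exact t calculation gives power 0.947 at 43 and 0.951 at 44, so 44 is reproduced. Hypothesis 4 therefore has at most 44 people, or about 40 after 10% loss (44 × 0.9 = 39.6).

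**3. Degrees of freedom.** Each person contributes one trait fatigue value, so the model is in effect an ordinary regression. With one term per listed predictor, residual df = 44 - 7 = 37. With age added, it is 36.

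**4. Size of the possible bias.** The documents give no correlation of age with heart rate variability, the other predictors or trait fatigue. All values below are assumptions. Let r₁ be the age/heart rate variability correlation and r₂ the age/trait fatigue correlation. Heart rate variability has no true effect.

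If the other five predictors are unrelated to age, omitting age gives heart rate variability a standardised coefficient of r₁ × r₂. If the others explain a share R² of the variance in trait fatigue, then
- p = |r₁r₂| / √(1 - R²)
- noncentrality = p√38 / √(1 - p²), where 38 = 44 - 6
- critical value of t on 37 df = 2.026

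Worked values:
- (-0.5, 0.3), R² = 0: p = 0.150, noncentrality 0.94, rejection 14.9%.
- (-0.5, 0.3), R² = 0.30: p = 0.150/0.837 = 0.179, noncentrality 1.12, rejection 19.4%.
- (-0.6, 0.4), R² = 0.30: p = 0.240/0.837 = 0.287, noncentrality 1.85, rejection 43.6%.

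**5. Simulation, including the case where other predictors also vary with age.** n = 44, 10,000 replicates per cell, rejection rate of the heart rate variability coefficient with age omitted. In the 30% columns, four of the five other predictors each have coefficient √(0.30/4) = 0.274.

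| (r₁, r₂) | Others unrelated to age, explain 0% | Unrelated, explain 30% | Others correlate 0.3 with age, explain 0% | Correlate 0.3, coefficients as for 30% |
|---|---|---|---|---|
| (-0.3, 0.2) | 6.8% | 7.6% | 5.9% | 5.5% |
| (-0.5, 0.1) | 6.0% | 6.1% | 5.6% | 8.4% |
| (-0.5, 0.2) | 9.4% | 11.2% | 7.5% | 6.2% |
| (-0.5, 0.3) | 15.4% | 19.5% | 10.1% | 5.2% |
| (-0.6, 0.4) | 30.7% | 43.0% | 19.3% | 5.6% |

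With age in the model, the rate was 4.8% to 5.4% in every cell.

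The last column shows what matters: the age effect left after the other predictors. There they carry 4 × 0.274 × 0.3 = 0.329 of the age/fatigue correlation. At r₂ = 0.3 this leaves -0.029, almost nothing. At r₂ = 0.1 it leaves -0.229, which is why that cell is higher than its neighbours.

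If the other predictors are unrelated to age but explain 50% of the variance, the rate at (-0.5, 0.3) rises to about 26%.

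**6. Walk-induced fatigue.** With an assumed correlation of 0.3 with age, and r₂ from 0.2 to 0.4, its rejection rate is about 5% to 11%, a smaller exposure than for heart rate variability.

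**The case against.** The strongest reply is that the omission is coherent. The only age rationale in the article is that attenuation and gating change with age. These are outcomes in Hypotheses 1 and 3 and predictors in Hypothesis 2, and they do not appear in Hypothesis 4. The rerun list matches that rationale exactly, so the plan does not contradict itself. This stands, although the article does not give it as the reason, and it does not remove the exposure. Hypothesis 2 also has a fatigue outcome, and its age rerun serves just the check that Hypothesis 4 lacks.

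It is also fair that Research Question 4 is described as exploratory, that the study is powered for Research Question 1a only, and that nothing in the documents says heart rate variability or trait fatigue varies with age in this population. These points limit the weight of the finding.

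Two stronger readings are tempting and should be resisted:
- A reader might infer that the heart rate variability result will be confounded, with a false-positive rate several times nominal. The documents do not support that. The same pair of assumed correlations gives 5% or 20%, depending on whether the other predictors carry the age gradient.
- A reader might infer that including Hypothesis 4 in the time-of-day and session-order rerun is misplaced, because trait fatigue is recorded before the sessions. That rerun is reasonable: both factors can affect the predictors measured in the sessions.

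**Conclusion.** The gap is certain from the text: Hypothesis 4 alone has no age-adjusted version, and neither its equation nor the between-group matching covers age. The consequence is conditional. It requires age to relate to a predictor and, beyond the other predictors, to trait fatigue. Under the assumed ranges (r₁ from -0.3 to -0.6, r₂ from 0.1 to 0.4, other predictors explaining up to 30% of the variance), the nominal 5% test rejects in about 5% to 44% of trials at n = 44. The upper end needs strong correlations and other predictors unrelated to age. With age included, the rate is about 5% throughout. This is an inexpensive improvement to an exploratory model. It does not show that the Hypothesis 4 result will be wrong, and it leaves the primary comparison untouched.

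**What to change.** In section 3.7.1, add Hypothesis 4 to the list of hypotheses rerun with age, and report the Hypothesis 4 coefficients with and without age side by side.

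Age is already collected. The cost is one of about 37 residual degrees of freedom. If age and heart rate variability are correlated at -0.5, the standard error of the heart rate variability coefficient also widens by a factor of about 1/√(1 - 0.25) = 1.15, before any gain from lower residual variance. Because this is a rerun, the unadjusted estimate is kept.

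No rule that an association counts only if it survives age adjustment is needed. The plan imposes none on the other hypotheses.
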